##### Spence Children’s Anxiety Scale

The Spence Children’s Anxiety Scale (SCAS) [31] is a self-report rating scale on which youths assess their symptoms of anxiety by answering 44 questions (including six positive filler items) on a 4-point scale. The scores are summed on six subscales reflecting symptoms specifically related to social phobia (six items), panic disorder and agoraphobia (nine items), generalized anxiety disorder (six items), obsessive-compulsive disorder (six items), separation anxiety disorder (six items), and fear of physical injury (five items). A total score reflects the overall severity of anxiety symptoms.

##### Parent version of the Spence Children’s Anxiety Scale

The parent version of the Spence Children’s Anxiety Scale (SCAS-P) [32] is a self-report rating scale on which parents assess their child’s symptoms of anxiety. It includes the same items as the SCAS but without the six filler items and is administered and scored like the SCAS. The Danish version of the SCAS and SCAS-P has demonstrated good psychometric properties [33].

##### Mood and Feelings Questionnaire

The Mood and Feelings Questionnaire (MFQ) [34] was developed to cover a broad range of cognitive and vegetative symptoms of depression in youths. The MFQ includes youth and parent versions (MFQ-P), consisting of 33 and 34 items, respectively, and each is rated on a 3-point scale. Studies show that the MFQ validly identifies children presenting with major depressive episodes, especially when the MFQ and the MFQ-P are used in combination. The Danish version of the MFQ has shown good psychometric properties [35].

##### Self-Efficacy Questionnaire for School Situations

The Self-Efficacy Questionnaire for School Situations (SEQ-SS) [18] was developed to assess the self-efficacy expectations of school-refusing youths. The SEQ-SS consists of 12 items and 2 subscales: academic/social stress and separation/discipline stress. Each item measures self-efficacy expectations related to different school situations on a 5-point scale. The total score is derived from summing the items together, yielding a total score. The SEQ-SS has been evaluated and shown to have good psychometric properties.

##### Personal Experience Checklist

The Personal Experience Checklist (PECK) [36] was developed to provide a multidimensional assessment of youths’ personal experience of being bullied, covering a full range of bullying behaviors, including covert relational forms of bullying and cyberbullying. The youths are asked to rate on a 5-point scale how often they have experienced different forms of bullying over the last month, and the scale consists of 32 items and 4 subscales: relational-verbal bullying, cyberbullying, physical bullying, and bullying based on culture. An evaluation of the PECK scale has shown that it provides a promising assessment of a child’s experience of bullying behavior.

##### Family Assessment Device

The Family Assessment Device (FAD) [37] was designed to assess different dimensions of family function. It is rated by both youth (over the age of 12) and parents. It consists of 3 subscales with a total of 60 statements describing various aspects of family functioning. This study will use the subscale for general functioning (12 items). The FAD has been evaluated as a good measure of overall family functioning with good psychometric properties [38].

#### Collaboration between family and school

Collaboration between family and school will be rated by the schools and parents. This will be rated on three questions:To what degree do you think that the cooperation between the school/teacher/family is working satisfactory?To what degree do you think that the teacher/family listens your suggestions for change?To what degree do you think that it is a good experience to talk to the teacher/family about your child/student?

These questions will be rated on a 4-point scale.

### Additional measures

#### Background information

Participating families will complete a background information questionnaire regarding family demographics, youth’s school and SA problems, youth’s mental and physical health, parents’ mental and physical health, and youth’s previous and ongoing treatment. Teachers complete information regarding the child’s academic function.

#### School Refusal Assessment Scale–Revised child version

The School Refusal Assessment Scale–Revised (SRAS-R) child version [39] was designed to evaluate the relative strength of four functional conditions of SR in youths: (1) avoid stimuli that provoke negative affectivity, (2) escape aversive social and/or evaluative situations, (3) pursue attention from significant others, and/or (4) pursue tangible reenforcers outside of school. The SRAS-R will be used as part of the assessment. The SRAS-R child version consists of a youth and parent version, both consisting of 24 items that are equally divided across the 4 functions and rated on a 7-point scale. The scale gives an indication of the strength of the four functional conditions of SR in the youths and is rated by both the youths and parents. The SRAS-R child and parent versions both have been shown to have good retest reliability and parent interrater reliability. A correlation between scores in SRAS-R child and parent versions has also been found.

#### Economic evaluation

The Child Health Utility 9D Index (CHU-9D) [40] was designed to determine how health affects children’s lives and is rated by the youth. The CHU-9D is a generic preference-based measure of health-related quality of life designed for the estimation of quality-adjusted life-years for economic evaluation of health care. It consists of nine dimensions (worry, sadness, pain, tiredness, annoyed feeling, schoolwork/homework, sleep, daily routine, and activities), each with five levels on which the child chooses the level fitting to how they are feeling. The instrument has previously been validated among children and adolescents in Great Britain and Australia, showing good psychometric properties [41, 42]**.** Socioeconomic data related to various background characteristics about children and parents and prospective data regarding grades, youth education, and employment will be extracted from Statistics Denmark’s registers and the registers of Aarhus Municipality and linked to survey data using the child’s civil registration number.

#### Treatment satisfaction

The revised version of the Experience of Service Questionnaire (ESQ), is used to assess satisfaction with the treatment [43]. The ESQ will be administered to youths, parents, and teachers at posttreatment (T2). There are separate versions for youths, with seven items, and parents and teachers, with ten items, including open questions for qualitative feedback.

#### Mediator measures

As shown in Table 3, to investigate possible mediators for an increase in school attendance, the SDQ, the SEQ-SS, and the SEQ-RSAP will be administered at sessions 3 and 7 during the intervention in the B2S group. For an overview of the schedule of enrollment, allocation, interventions, and assessments, please *see* Fig. 2 for the completed Standard Protocol Items: Recommendation for Interventional Trials (SPIRIT) figure.

**Table 3 Tab3:** Overview of mediator measures, and assessment points for participants in B2S condition

Measure	Respondent	Time	
		S-3	S-7
SDQ	Y, P	●	●
SEQ-SS	Y	●	●
SEQ-RSAP	P	●	●

*Abbreviations: P* Parent, *SCAS* Spence Children’s Anxiety Scale, *SDQ* Strength and Difficulties Questionnaire, *SEQ-RSAP* Self-Efficacy Questionnaire for Responding to School Attendance Problems, *SEQ-SS* Self-Efficacy Questionnaire for School Situations, *Y* Youth

**Fig. 2 Fig2:**
[figure not shown]
Standard Protocol Items: Recommendation for Interventional Trials (SPIRIT) diagram of schedule of enrollment, allocation, interventions, and assessments

### Sample size

On the basis of findings of recent meta-analyses of both truant SA [10] and SR SA [11], we expect to find a standardized effect size regarding SA in the range of 0.46–0.54. The targeted sample size is 70 per condition to provide sufficient statistical power (0.80) and a significance level (0.05, two-tailed) to find a generalized effect size regarding SA of 0.54. Similar RCTs have a mean attrition rate of 10% [44–47]; therefore, 80 participants are included in each condition (B2S *n* = 80, TAU *n* = 80).

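### The sample-size figures do not fit together: 80% power at d = 0.54 needs 55 per arm, and the stated 70 per arm gives about 89% at 0.54 or 80% at about 0.48

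*Protocol article*

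**What the plan says.** The Sample size section of the protocol article takes its effect sizes from two meta-analyses, one of truancy and one of school refusal, and says "we expect to find a standardized effect size regarding SA in the range of 0.46–0.54". The Background attributes g = 0.46 to the truancy review and g = 0.54 to the school refusal review.

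The section then fixes the size: "The targeted sample size is 70 per condition to provide sufficient statistical power (0.80) and a significance level (0.05, two-tailed"), and the purpose is "to find a generalized effect size regarding SA of 0.54". Only after that does it bring in a 10% attrition rate, which takes the 70 to 80 randomised per condition. It names no test. It mentions no adjustment for clustering, multiplicity or repeated measures.

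**The concern.** Sample size, power, significance level and effect size are given as one set. Once three are fixed the fourth follows, so a reader can check the set, and on the usual two-sample calculation it fails. Seventy per arm is clearly more than 0.54 requires at 80% power.

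A reader who takes the sentence at face value will believe that 0.54 is the smallest effect the trial detects with 80% power. The actual figure for 70 per arm is about 0.48. The section also quotes power only at the upper end of its own expected range, so the reader cannot tell from it what power the trial has at 0.46.

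**Working it through.** **Inputs, all from the Sample size section.** Effect d = 0.54 (range 0.46 to 0.54, in SD units, so SD = 1); two-sided alpha 0.05; power 0.80; 70 per arm before attrition; 10% attrition; 80 per arm randomised, 1:1. **Assumption:** a two-sample comparison of means, because the section names no test.

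**Step 1. Try to reproduce 70.** In the normal approximation, n per arm = 2(z₀.₉₇₅ + z₀.₈₀)² / d².

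- (1.960 + 0.842)² = 7.849, and twice that is 15.70.
- At 0.54: 15.70 / 0.2916 = 53.8, so 54. The noncentral t gives 54.8, so 55.
- At 0.46: 15.70 / 0.2116 = 74.2, so 75. The noncentral t gives 75.2, so 76.

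The stated 70 is not reproduced at 0.54. It exceeds the requirement by a factor of 70/55 = 1.27.

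**Step 2. Power for the numbers planned.** In the normal approximation, power = Φ(d√(n/2) − 1.960). For n = 70, √35 = 5.916.

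- At 0.54: Φ(3.195 − 1.960) = Φ(1.235) = 0.892.
- At 0.46: Φ(2.721 − 1.960) = Φ(0.761) = 0.777.

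The noncentral t gives slightly lower values:

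| Analysed per arm | Power at 0.54 | Power at 0.46 | Effect detectable at 80% |
|---|---|---|---|
| 70 (stated target) | 0.887 | 0.771 | 0.477 |
| 72 (80 less 10%) | 0.896 | 0.783 | 0.470 |
| 80 (all randomised) | 0.924 | 0.824 | 0.446 |

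**Step 3. Effect that matches 70 at 80% power.** (1.960 + 0.842) × √(2/70) = 2.802 × 0.1690 = 0.474 in the normal approximation, and 0.477 by the noncentral t. Rounded up, 0.48.

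**Step 4. Look for another route to 70 at 0.54.** None of these variants gives it:

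- One-sided 0.05: 44 per arm.
- Power 0.85: 63 per arm. Power 0.90: 74 per arm.
- Two-sided alpha 0.025, as in a split over two primary measures: 67 per arm.
- Rank-test efficiency of 0.955 or 0.864: 55/0.955 = 57.6, so 58; 55/0.864 = 63.7, so 64.
- Attrition: the section applies it after the 70. 70/0.9 = 77.8, so 78, and 80 covers it.

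**Step 5. How much loss matters at 0.46.** 80% power there needs 76 analysed per arm. From 80, that allows 4 losses per arm, or 4/80 = 5%.

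**The case against.** Four points can be made for the article.

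1. *The error is on the safe side.* The aim is phrased as "to provide sufficient statistical power (0.80"). Read as at least 0.80, that is met at 0.54 with room to spare. This stands, and it limits the seriousness. It does not make 70 the number that follows from the stated inputs.

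2. *The design is not short at 0.46.* A reader might infer from the 77% that the trial misses 80% power for part of its expected range and that the section conceals this. The documents do not support that reading. The plan randomises 80 per arm. Daily absence data come from the municipality and reporting is mandatory for public schools (Primary outcome); the larger attrition expected in the usual-care arm is tied to the secondary measures (Participants, recruitment, and eligibility criteria); and withdrawn participants are analysed as randomised (Statistical analysis). If all 80 contribute, power at 0.46 is 82%. The range and the design value are also printed openly in adjacent sentences. One reservation remains: attendance is also measured by parent report, which can lose participants, so full retention is not assured on both measures.

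3. *The benchmark is assumed.* The planned analysis is a mixed linear model over T1 to T3 with a group-by-time interaction (Primary study parameters), so 70 might come from a calculation the article does not print. That is possible, and a condensed article need not print every detail. But the inputs that it does print do not lead to 70.

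4. *Rounding.* The article seems to favour round numbers: 77.8 became 80. Rounding could carry 67, the figure for an alpha of 0.025, to 70. The section, however, states alpha as 0.05, and rounding does not carry 55 to 70.

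**Conclusion.** The stated set of 70 per arm, power 0.80, two-sided 0.05 and d = 0.54 is wrong as written. For a two-sample comparison, 0.54 needs 55 per arm. Seventy per arm gives about 89% power at 0.54, some 9 points above the stated figure, and 80% at about 0.48.

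The error is conservative at the effect the trial was sized for, so it does not support a claim that the trial is underpowered. At 0.46, power runs from 77% (70 analysed) through 78% (72) to 82% (80). The shortfall is at most about 3 points over these numbers and disappears if no more than 4 of 80 per arm are lost. Choosing the upper end of the range as the design value is an openly stated choice, not an arithmetic error.

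These figures assume a two-sample comparison of means with equal arms and no clustering or multiplicity adjustment, since the section states none. This is a minor correction: it changes how the detectable effect is read, not the size or conduct of the trial.

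**What to change.** Keep 80 per arm and replace the power sentence. For example:

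> *70 analysable per arm give 80% power (two-sided 5%, two-sample comparison) for d = 0.48; power is 89% at 0.54 and 77% at 0.46 (82% at 0.46 if all 80 per arm are analysed).*

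If the 70 came from another calculation, such as one for repeated measures, clustering or a split significance level, state that calculation and its inputs instead.

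The cost is one sentence. No participants are added and the analysis does not change. The only less favourable consequence is that the power at 0.46 appears in print.

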### Statistical analysis

Analyses will be undertaken on an intention-to-treat basis. Any participants who are randomized but withdraw from the study will be included in the analysis as randomized.

#### Primary study parameters

Mixed linear models (MLMs) will be used to compare groups (B2S and TAU) over time (T1, T2, T3) for all recurrent outcome variables. Later, the same analyses will be performed for the follow-up period (T3, T4). MLMs will be used to measure main effects of group and time and the time × group interaction effects. MLMs tolerate missing values and thus do not unnecessarily compromise statistical power [48]. All MLMs will be estimated with the maximum likelihood method and based on the intention-to-treat sample. All models will include a random intercept, and the slope will be specified as random if improving the model fit evaluated by a significant change in the -2 log-likelihood (- 2LL) fit statistics [49]. A visual inspection of the data and an inspection of the model indices for the time variable will determine the best fit for the time variable. The outcomes of specific problems of relevance in the corresponding subgroups having anxiety, depression symptoms, or behavior problems as their primary problems will be explored.

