Some children with problematic SA display anxiety and/or depression; some display externalizing problems, some display both, and some display other problems, (e.g., at a family or school level). In addition, negative cognitions concerning the ability to cope with situations associated with school attendance have been shown to be prevalent among children with problematic SA [18, 19]. Self-efficacy concerning school situations has been found to increase following treatment, and treatment that increases self-efficacy may reduce anxiety, depression, and behavior problems and facilitate reengagement with schooling [20].

An intervention that addressed the needs of this very heterogeneous group therefore needs to be based on an initial assessment and case formulation, followed by a modular, transdiagnostic approach that includes evidence-based interventions for anxiety, depression, behavior problems, parent training and teacher training, and a focus on increasing self-efficacy.

The main objective of this study is to test the efficacy of Back2School (B2S) [21], a modular transdiagnostic CBT intervention aimed at increasing school attendance and decreasing anxiety, depression, and behavior problems among youth with problematic SA. The study uses an RCT design with an active control group receiving treatment as usual (TAU). Based on previous studies, our primary hypothesis is that the B2S intervention will be superior to TAU in improving school attendance. Secondary hypotheses are that the B2S intervention will be superior to TAU in reducing anxiety, depression, and behavior problems. We further hypothesize that improvement in school attendance will be mediated by reductions in the youths’ anxiety, depression, and behavior problems and increases in the youths’ and parents’ self-efficacy. Other members of our research team will perform an economic evaluation comparing the B2S group with the TAU group, both in terms of cost utility measured with a quality-of-life measure and in terms of cost benefit measured by subsequent obtained grades, youth education, employment, and income.

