## Methods/design

### Study design

The study is a randomized controlled, parallel group, superiority trial that compares TAU with a modular transdiagnostic CBT intervention (B2S) for SA in youths aged 7–16 years. The design is a two (Back2School and TAU) by four (preassessment [T1], postassessment [T2], and 3-month [T3] and 1-year [T4] assessments) mixed between-within design. The overall study design is illustrated in Fig. 1.

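### The follow-up model covers only T3 and T4, and none of its named terms, as usually coded, is the B2S–TAU difference at 1 year

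*Protocol article*

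**What the plan says.** The Study design section sets out a two-arm, four-occasion "mixed between-within design", the occasions being "preassessment [T1], postassessment [T2], and 3-month [T3] and 1-year [T4] assessments". The Background section states that "our primary hypothesis is that the B2S intervention will be superior to TAU in improving school attendance" and names no time point.

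The analysis is then split under Primary study parameters. First: "Mixed linear models (MLMs) will be used to compare groups (B2S and TAU) over time (T1, T2, T3) for all recurrent outcome variables". Second: "Later, the same analyses will be performed for the follow-up period (T3, T4)". The inferential terms are the same for both: "MLMs will be used to measure main effects of group and time and the time × group interaction effects". How time is coded is not fixed in advance; it is to be chosen after looking at the data and at how well the model fits.

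The article states no model spanning T1 to T4, no baseline covariate in the follow-up model, and no contrast at T4.

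**The concern.** In the T1–T3 model the group-by-time interaction is a natural test of treatment, because T1 precedes treatment and the arms start equal by randomisation. Running the same analysis on T3 and T4 changes what each term means. Both occasions now follow treatment, so the interaction tests only whether the arms diverge or converge further after T3. The group main effect blends the 3-month difference with the 1-year difference.

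The 1-year assessment is the trial's longest follow-up, and readers will want one number from it: how far apart the arms are at 1 year. As written, the plan leads the analyst to report two other numbers. If only one is picked up, a fully maintained benefit can be described as no effect over follow-up (null interaction), or a benefit that has faded as a follow-up effect (significant group term).

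**Working it through.** The article gives no power or effect size specific to the 1-year analysis, so there is no figure of its own to reproduce first.

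**Inputs**
- Children per arm: 80 less the 10% attrition in the Sample size section, 80 × 0.90 = 72.
- Two-sided 5% level, from the same section.
- Effect: 0.5 SD, inside the section's expected range of 0.46–0.54.
- Assumed, not in the document: within-child correlation ρ of 0.3, 0.5 or 0.7, equal between all occasions, and SD 1 at each occasion. Outcome scored so that higher means better attendance; the sign reverses if absence is analysed.

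**What the terms estimate.** Let D3 and D4 be the B2S–TAU differences at T3 and T4. With centred (effect) coding of time:
- group main effect = (D3 + D4)/2
- interaction = D4 − D3
- 1-year difference D4 = main effect + ½ × interaction

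The group coefficient depends on coding: it is D3 if T3 is the reference and D4 if T4 is. Random-intercept models fitted to 4,000 simulated children (true D3 = 0.54, D4 = 0, ρ = 0.5) showed this. The group coefficient was 0.24 centred, 0.50 with T3 as reference and −0.01 with T4 as reference; the interaction was −0.51.

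**Standard errors**, n = 72 per arm, √(2/n) = 0.1667:
- main effect: 0.1667 × √((1+ρ)/2) = 0.134, 0.144, 0.154 for ρ = 0.3, 0.5, 0.7
- interaction: 0.1667 × √(2(1−ρ)) = 0.197, 0.167, 0.129
- T4 difference, unadjusted: 0.167
- T4 difference, adjusted for T1: 0.1667 × √(1−ρ²) = 0.159, 0.144, 0.119

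**Probability of a significant result** (t-based)

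| Scenario and term | True value | ρ = 0.3 | ρ = 0.5 | ρ = 0.7 |
|---|---|---|---|---|
| Maintained (D3 = D4 = 0.5): interaction | 0 | 5% | 5% | 5% |
| Maintained: group main effect | 0.50 | 96% | 93% | 90% |
| Maintained: T4 difference, unadjusted | 0.50 | 85% | 85% | 85% |
| Maintained: T4 difference, adjusted for T1 | 0.50 | 88% | 93% | 99% |
| Vanished (D3 = 0.5, D4 = 0): group main effect | 0.25 | 46% | 40% | 37% |
| Vanished: interaction | −0.50 | 71% | 85% | 97% |
| Vanished: T4 difference, either form | 0 | 5% | 5% | 5% |

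**Both terms read together.** With equal variances the covariance of the two estimates is (Var D4 − Var D3)/2 = 0, so they are independent. If the benefit has vanished, a significant group effect with no significant interaction to warn of it has probability 0.455 × (1 − 0.712) = 13% at ρ = 0.3, 0.405 × (1 − 0.846) = 6% at ρ = 0.5, and 0.366 × (1 − 0.970) = 1% at ρ = 0.7.

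**Who is left out.** A child with T1 or T2 data but neither T3 nor T4 contributes nothing to a T3–T4 model. In a T1–T4 model the child's earlier values still inform the estimates under a missing-at-random assumption.

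**The case against.** The strongest reply is that the plan names all three terms, and together they tell the right story most of the time. A significant group effect with a null interaction is the proper signature of a maintained benefit, and the group term detects it with 90–96% power. If the benefit has faded, the interaction usually says so. This stands, and it rules out a stronger reading that a reader might infer: that the 1-year conclusion will be wrong in both directions. That follows only if one named term is read and the other ignored.

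A second reply is that the 1-year difference is not out of reach. It is the main effect plus half the interaction, or the group coefficient if T4 is the reference, and the article leaves the coding open. This also stands. The claim is therefore that no named term in its usual coding is that difference, not that the model cannot yield it.

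Third, omitting T1 causes no bias when data are complete. Allocation is random and stratified on amount of absence and on grade group (Randomization), so an unadjusted T4 difference is valid and the cost is precision.

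Fourth, loss of data matters less for the primary outcome, since absence registration is mandatory and supplied by the municipality (Primary outcome). Some registry loss at T4 is foreseeable for pupils who finish ninth grade, but it is driven by grade. The point applies mainly to questionnaires, for which the article itself expects more attrition under TAU.

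Finally, the follow-up model may be meant only to describe maintenance, and contrasts are often left to an analysis plan. But the article fixes the occasions as T3 and T4, and an analysis plan that wanted a baseline-adjusted 1-year effect would have to depart from that.

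**Conclusion.** The point holds in a limited form and should be fixed, without being critical. The article fixes a follow-up model on T3 and T4 whose named terms, as usually coded, do not include the 1-year treatment difference, although the design measures both arms from T1 to T4. Read alone, the group term is significant in about 37–46% of trials when nothing is left at 1 year, and the interaction is zero by construction when everything is kept. Read together, the chance of a group effect with no warning interaction falls to about 1–13%. Leaving out T1 lowers power for a maintained 0.5 SD difference at T4 to 85%, against 88–99% with adjustment.

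The meaning of the terms is algebra and needs no assumption. The percentages rest on 72 per arm, a 0.5 SD effect, and the assumed equal correlation of 0.3–0.7. The document does not support a claim of bias or of a generally misleading 1-year result. The T1–T3 analysis is unaffected.

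**What to change.** Keep the T1–T3 analysis and report it first, as planned. When T4 is complete, replace the separate T3–T4 model with one mixed model on T1, T2, T3 and T4, with time as a category. Name the baseline-adjusted B2S–TAU difference at T4 as the 1-year effect, for example by giving both arms a common mean at T1. Report the T4-minus-T3 change in the group difference only as a description of maintenance.

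Say baseline-adjusted rather than change from baseline. Under the assumptions above, the T1-to-T4 change contrast has the same standard error as the T3–T4 interaction, so its power for 0.5 SD would be 71–97%, against 88–99% for the adjusted difference.

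The cost is a few sentences in the analysis plan and slightly more analysis work, with the same data and the same class of model.

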### Randomization

Randomization to treatment condition will be conducted using a computer-generated random digit procedure with two possibilities (B2S and TAU). Treatment outcome of school absence may be affected by the age of participants and the amount of school absence. Therefore, to ensure balanced groups, the randomization will be stratified on the presence of two factors, *age* (first to fourth grade [younger] or fifth to ninth grade [older]) and *amount of school absence* (< 50% [low] or > 50% absence [high]). To maintain similar treatment group sizes, the randomization will be conducted using permuted block randomization. The randomization is administered by staff outside the research group.

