#### Therapists

School psychologists from Aarhus Municipality and clinical psychologists from CEBU will conduct the B2S intervention together with a clinical psychology graduate student at CEBU as cotherapist. There is one psychologist and one cotherapist per case. All therapists and cotherapists receive a 6-day training course and four 1-day brush-up courses regarding assessment, case formulation, and the B2S and MMM manuals. In total, therapists and cotherapists receive 80 h of training. All therapists and cotherapists receive weekly face-to-face group case supervision by specialists in clinical child psychology.

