#### Primary outcome

The primary outcome is school attendance, which is measured in two ways:It is mandatory for all public schools in Denmark to report school absence data for all schoolchildren on a daily basis. Daily school absence data for youth included in the study will be provided by Aarhus Municipality. Absence data 1 year prior to the youths’ inclusion in the project and at follow-up are also provided by the municipality.Retrospective daily school absence for a 2-week period (10 schooldays) is reported by parents at all assessment points (as part as the assessment battery at preassessment, postassessment, and follow-up).

In addition, the families in the B2S group will register daily absence for each lesson throughout their course in the B2S intervention.

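### Treating T1 as a free outcome makes the time × group test a change-score comparison: valid, but less precise than adjusting for baseline

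*Protocol article*

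**What the plan says.** **Model.** In the protocol article, Primary study parameters, mixed linear models compare the arms over T1, T2 and T3, and "MLMs will be used to measure main effects of group and time and the time × group interaction effects". Every model has a random intercept. A random slope is added if it improves the fit, and the coding of time is left to inspection of the data.

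**Baseline data.** Table 2 lists registry absence at T1 in both arms. The Primary outcome section adds that the municipality supplies earlier records: "Absence data 1 year prior to the" child's inclusion.

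**Stratification.** The Randomization section gives the reason for stratifying: "Treatment outcome of school absence may be affected by the age of participants and the amount of school absence". The grade strata are "first to fourth grade [younger] or fifth to ninth grade [older", and the absence strata are below 50% and above 50%. The section on participants, recruitment and eligibility admits grade 0 through grade 9 (except the last semester of grade 9).

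**Sample size.** The Sample size section targets 70 per condition, with "sufficient statistical power (0.80" and "significance level (0.05, two-tailed" in brackets, "to find a generalized effect size regarding SA of 0.54". The expected range of the effect is 0.46 to 0.54.

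**Delivery.** In Back2School, "There is one psychologist and one cotherapist per case". The number of therapists and their caseloads are not given.

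**The concern.** Randomisation makes the arms equal in expectation at T1. A model that estimates a separate T1 mean for each arm does not use that fact. The treatment effect becomes the difference between arms in mean change, which carries the full noise of the T1 measurement. When T1 predicts the later outcome only moderately, this costs precision, and below a correlation of 0.5 it is worse than ignoring T1 altogether.

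Power is at stake. The protocol allows that the true effect may be as low as 0.46. At that value the form of the baseline adjustment can decide whether the 0.80 target is met. The data needed for the better analysis are already being collected.

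**Working it through.** **Inputs from the Sample size section:** 70 per arm, two-sided alpha 0.05, d = 0.54 (powered) and d = 0.46 (low end of the range). **Assumed, because the documents do not give it:** T1-to-post correlation rho = 0.3, 0.5 and 0.7.

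**1. The plan's own figure.** A two-sample t-test at d = 0.54 and 80% power needs 55 per arm (54 by the normal approximation), not 70. With 70 per arm, power is 89% at d = 0.54 and 77% at d = 0.46. That mismatch is a separate matter; 70 is used here as given.

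**2. Variance of the treatment contrast**, one pre and one post measure, unit SD:
- free baseline (change score): proportional to 2(1 − rho)
- baseline-adjusted or common T1 mean: proportional to 1 − rho²
- ratio: 2(1 − rho)/(1 − rho²) = 2/(1 + rho), which is 1.54, 1.33 and 1.18 at rho = 0.3, 0.5 and 0.7

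A comparison of post scores alone has variance proportional to 1, so the change score is the worse of those two whenever 2(1 − rho) > 1, that is, rho < 0.5.

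**3. Power at 70 per arm.** Effective d is d/√(2(1 − rho)) for the change score and d/√(1 − rho²) for the adjusted contrast, put into the noncentral t with 138 df.

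| d | rho | effective d, change | effective d, adjusted | power, change | power, adjusted |
|---|---|---|---|---|---|
| 0.54 | 0.3 | 0.456 | 0.566 | 76.5% | 91.4% |
| 0.54 | 0.5 | 0.540 | 0.624 | 88.7% | 95.6% |
| 0.54 | 0.7 | 0.697 | 0.756 | 98.4% | 99.4% |
| 0.46 | 0.3 | 0.389 | 0.482 | 62.7% | 80.9% |
| 0.46 | 0.5 | 0.460 | 0.531 | 77.1% | 87.7% |
| 0.46 | 0.7 | 0.594 | 0.644 | 93.7% | 96.6% |

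The normal approximation gives values at most 0.6 points higher.

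**4. Does this carry over to three occasions?** Sixty simulated trials (70 per arm, T1 to T3, time categorical, random intercept, maximum likelihood) had between- and within-participant variance of 0.5 each and a two-level stratum shifting all occasions by 0.8. The implied rho is (0.5 + 0.16)/1.16 = 0.57. The mean standard error of the T2 contrast was 0.166 with a free baseline and 0.147 with a common T1 mean. The variance ratio is (0.166/0.147)² = 1.28, against 2/(1 + 0.57) = 1.27 from the formula.

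**5. Stratification factors.** In the same simulation, a stratum main effect added to the free-baseline model changed the time × group estimate by less than 1e-14 and left its standard error at 0.166. A term that is constant over time drops out of a change. Added to the constrained model, it lowered the standard error from 0.147 to 0.144. In the free-baseline model only stratum × time terms could act on the contrast, and that gain was not quantified.

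**6. Strata against eligibility.**

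| | Eligibility | Randomization strata | Not covered |
|---|---|---|---|
| Grade | 0 to 9 | 1 to 4; 5 to 9 | grade 0 |
| Absence | above 10% | below 50%; above 50% | exactly 50% |

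**The case against.** The strongest reply is that the planned test is sound. A free T1 gives an unbiased contrast with correct standard errors, and at d = 0.54 with rho = 0.5 it has 89% power, above the 80% sought. The size of the loss depends on a correlation that the article does not report, and the loss is small at 0.7. Registered absence is not ignored either, since T1 is in the response. All of this stands. It makes the point one of efficiency; it does not make the free form preferable, because the adjusted contrast is at least as precise throughout the range examined.

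Two stronger readings are tempting. The first is that leaving out the strata distorts standard errors or loses power. Stratum main effects do not alter the time × group contrast (step 5). The known conservatism from omitting strata belongs to a comparison of post-treatment values, which is not the test described here.

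The second is that ignoring therapist clustering makes the standard errors too small. The direction is right in principle. But the article gives no intraclass correlation, caseload or number of therapists, and treatment as usual is itself usually delivered by school psychologists. With an assumed correlation of 0.01 to 0.10 and 5 to 14 cases per therapist in Back2School only, true type I error would run from 5.2% to 12.7%, which is too wide a range to support a conclusion.

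For both, the article is silent and does not exclude the terms. Covariates and higher-level random effects are commonly left to an analysis plan.

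**Conclusion.** The point holds as an efficiency improvement. The article fixes T1 as an outcome with a free group effect, and the resulting contrast has 1.18 to 1.54 times the variance of a baseline-adjusted one for rho from 0.7 down to 0.3. At d = 0.46 the planned form falls short of 80% power at rho = 0.3 and 0.5, while the adjusted form reaches it; at rho = 0.7 both do. These figures rest on the assumed rho, 70 evaluable per arm, equal variances at the two occasions, and a pre-to-post contrast; a linear coding of time or a random slope would change them somewhat.

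A reader might infer that the planned error bars are wrong. The documents do not support that: the free baseline costs precision only, and the therapist question cannot be sized from what is given.

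The gap between the strata and the eligibility criteria is a real inconsistency that needs no assumption, but it is a minor matter of wording.

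**What to change.** 1. State the primary contrast as baseline-adjusted. Either drop the group main effect at T1 so that the arms share a common T1 mean, or use pre-randomisation registered absence as a covariate with only post-randomisation occasions as outcomes. The common-mean constraint is justified at T1 only; it should not be carried to T3 in the later T3–T4 analysis.
2. Include grade group and absence level, each with its time interaction.
3. Reconcile the stratum definitions with eligibility so that grade 0 and exactly 50% absence each fall in a stratum. Inclusion began in September 2017, so the wording should record how randomisation was actually run, and the analysis should use those same strata.
4. As a sensitivity analysis only, fit a therapist random effect in the Back2School arm.

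The cost is a change of wording and a few degrees of freedom. The outcome and stratum data are already collected; the therapist analysis needs only a record of who treated whom.
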